#### Enrollment and Interventions

The attending physician will provide a complete written explanation and obtain written consent from patients who meet the inclusion criteria. Subsequently, the attending physician will perform subject registration after confirming that the patients meet all the inclusion criteria and none of the exclusion criteria by performing prespecified medical tests.

### Procedures

#### Time Point: Enrollment (4 Weeks Before the Study to the Start of the Study)

An eligibility screen will be conducted and informed consent will be provided to those who are eligible. The following assessments will be carried out: the SDS (ie, the tool that is used for tracking changes in depressive symptoms over time during the course of a study and after treatment [35]) and physical examination findings (ie, height, weight, abdominal circumference, blood pressure, and heart rate). In addition, smoking status and exhaled carbon monoxide (CO) levels will be determined, and subject background data will be collected, including age; sex; medical history; comorbidities; presence or absence of allergies; subjective symptoms; drinking patterns, regarding subjects who drink daily or 3 to 4 times a week, and alcohol consumption, which is monitored and reported in converted values; sleep duration; smoking index (ie, the number of cigarettes smoked per day × years of tobacco use); nicotine dependence, measured by the Tobacco Dependence Screener and the FTND; and the subject’s first medication for smoking cessation.

#### Time Point: Allocation (Day of Treatment Start)

##### Procedures

We will commence the following standard smoking cessation and aromatherapy programs for patients who have provided informed consent. In principle, a sufficient amount of time will be allowed for briefing the subjects to facilitate a complete understanding of the content of this study. Subsequently, their informed consent will be obtained. The maximum duration of obtaining informed consent after briefing is 4 weeks. However, if it is confirmed that the subject has sufficiently understood the content of the briefing, their informed consent may be obtained on the day of the briefing. The standard smoking cessation program was administered according to the Standard Procedure Manual for Anti-Smoking Treatment, which was originally issued in March 2006 by the Japanese Circulation Society, the Japan Lung Cancer Society, and the Japanese Cancer Association. Treatment consists of pharmacotherapy with transdermal nicotine patches and oral varenicline as well as nonpharmaceutical therapy with counseling by doctors and nurses. The patients were examined on their first visit and after 2, 4, 8, and 12 weeks (ie, 3 months) while being treated with transdermal nicotine patches or oral varenicline.

##### Aromatherapy

The following aromatherapy program will be provided in this clinical trial. Subjects will choose from four essential oils: black pepper, lavender, peppermint, and citrus (ie, lemon and grapefruit). These essential oils have been used in previous smoking cessation studies, were reported to have antidepressant and anxiety-reducing effects, and are readily available. Black pepper has been used in previous smoking cessation studies [24], while lavender has antianxiety and antidepressant effects [27]. Moreover, peppermint also has a mechanism of action that suggests a therapeutic effect in people with depression [29]. Limonene is reported to increase dopamine levels in the brain [28], similar to how dopamine is released during smoking [36]; all the essential oils selected for this study contain limonene [37-40]. The aromatherapist will provide subjects with an inhaler filled with their chosen oil; subjects will smell these for 10 to 20 seconds 3 times a day (ie, after breakfast, lunch, and dinner) and at other personally preferred times (ie, when their urge to smoke increases or when they feel anxious). The essential oils and inhalers are produced by Mont Saint Michel, Sanritsu Corporation, Osaka, Japan.

##### Profile of Mood States

We will collect the POMS self-assessment sheets completed by the patients. The short version of the POMS is a tool that facilitates understanding of subjects’ current moods, emotions, and changes, with little effort required from the subjects [41]. Self-assessment tests—the SDS and the POMS—will be completed by the subjects. In case of any omissions or obvious errors detected, the medical staff will ask for the information verbally. 

##### Blood Tests

We will analyze subjects’ baseline clinical data by performing blood tests (ie, blood glucose, hemoglobin A_1c_, low-density lipoprotein cholesterol, high-density lipoprotein cholesterol, triglyceride, uric acid, sodium, potassium, creatinine, glutamic-oxaloacetic transaminase, glutamic-pyruvic transaminase, alkaline phosphatase, g-glutamyl transpeptidase, creatine phosphokinase, C-reactive protein, and complete blood count). We will determine whether or not patients are taking antihypertensive drugs, dyslipidemia drugs, oral diabetes drugs, insulin, sleep medication, or other drugs, specifically anticancer drugs, drugs for hormonal treatment, and steroids.

#### Time Point: 2, 4, 8, and 12 Weeks

We will check for any adverse event and list its grade according to the CTCAE (version 4.0). Aromatherapy adherence status will be rated as follows:

Good: the aromatherapy inhaler is used nearly every day (approximately 80% of the days)Somewhat poor: the aromatherapy inhaler is not used on some days (approximately 60% of the days)Poor: the aromatherapy inhaler is not used on most days (approximately 30% of the days).

SDS scores, physical examination findings (ie, height, weight, abdominal circumference, blood pressure, and heart rate), smoking status, and exhaled CO levels will also be monitored. Further, in weeks 4 and 12, we will collect the POMS self-assessment sheets completed by the patients. At 12 weeks, we will perform the blood tests and perform a confirmation of smoking cessation. We will determine whether or not patients are taking antihypertensive drugs, dyslipidemia drugs, oral diabetes drugs, insulin, sleep medication, and other drugs, specifically anticancer drugs, drugs for hormonal treatment, and steroids. If a subject does not arrive for a scheduled visit, the reason for their absence will be discussed via a phone call. When the reason is hesitation or the unwillingness of a subject to visit the smoking cessation clinic, they will be requested by medical doctors or nurses to visit the hospital. This strategy is described in the Standard Procedure Manual for Anti-Smoking Treatment, which was originally issued in March 2006 by the Japanese Circulation Society, the Japan Lung Cancer Society, and the Japanese Cancer Association (Figure 1).

**Figure 1 figure1:**
[figure not shown]
Schedule for observations and tests. "X" indicates that the study task or assessment was performed at the indicated time point. CO: carbon monoxide; POMS: Profile of Mood States; SDS: Zung Self-Rating Depression Scale.

#### Study Period

The observation period (ie, follow-up) will last 3 months after the enrollment of the last subject, and the total study period will amount to 2 years and 3 months; the scheduled period was expected to run from July 2019 to September 2021. Since the number of subjects decreased due to the COVID-19 pandemic, the study period was extended to 3 years and 3 months on May 17, 2021, with the approval of the Institutional Review Board (IRB); the study is now expected to run until September 2022.

### Primary Outcome, Secondary Outcomes, and Procedures

#### Primary Outcome

The primary outcome is the change in SDS and POMS scores [35,41] (ie, depression assessment following smoking cessation), which will be evaluated for the period from the pretreatment screening to 4 weeks and 12 weeks after the start of aromatherapy.

#### Secondary Outcomes

The secondary outcomes are as follows:

Successful smoking cessation rate. The percentage of subjects who stop smoking 12 weeks after aromatherapy (ie, the number of subjects who stop smoking divided by the total number of allocated subjects, as a percentage). Successful smoking cessation refers to a report of smoking cessation for the past 7 days and an exhaled CO level below 7 ppm [42].Changes in body weight, abdominal circumference, and glycolipid metabolism (ie, assessment of obesity following smoking cessation and dyslipidemia).Adverse events during the period of aromatherapy.Blood cell counts and biochemical tests by blood sample collection.Other laboratory findings or symptoms.Correlation between essential oil preference and smoker information items at first-time visit (ie, day of treatment start). Smoker information items include the following subject background data: age, sex, BMI, number of tobacco pieces consumed or smoked per day, FTND scores, and SDS and POMS scores. These items will be compared among different essential oil types.Changes in essential oil preferences over time.

### Statistical Analysis

Research on the efficacy of aromatherapy as an adjuvant therapy for smoking cessation is scarce. Further, based on our research, the size of the effects of aromatherapy on psychological tests as measured by the SDS and the POMS in smokers has never been reported. Therefore, this study was designed as a pre-post single-arm clinical trial in which the sample size has been determined by considering the feasibility of registration. We will perform a comparison of the aromatherapy group with the standard treatment group from our previous study, “A Randomized, Multi-center, Double-Blind, Placebo-Controlled Trial for the Effects of Yokukansan on Depressive or Neurotic Smoking Patients during Smoking Cessation Therapy” (UMIN ID: 000027036). Similar to this aromatherapy study, the yokukansan study targeted the population of “depressed smoking patients.” For the yokukansan study, 100 patients were registered in our hospital.

Assuming that the registration number of this aromatherapy study would be comparable to that of the previous yokukansan study, this study planned to register 100 patients. The SDS scores and POMS subscale scores at baseline and at the 12-week time point will be compared using paired-samples *t* tests in the aromatherapy group of this study and in the standard treatment group of our previous study. Statistical significance was set at *P*<.05. Furthermore, concerning changes in data from baseline to the 12-week time point, a two-way analysis of variance will be used analyze the interaction between the standard treatment group and the aromatherapy group. The same will be used to compare changes in SDS and POMS scores before and after smoking cessation between the historical control group and the aromatherapy group of this study.

We will also compare the successful smoking cessation rates for a period of 12 weeks from the start of treatment between the standard treatment group and the aromatherapy group. Successful smoking cessation refers to a report of smoking cessation for the past 7 days and an exhaled CO level below 7 ppm. The successful smoking cessation rate was calculated by dividing the number of subjects who successfully stopped smoking 12 weeks after smoking cessation treatment by the total number of subjects who provided consent and received the treatment, multiplied by 100 to give the percentage. Descriptive statistics on subjects’ background data will be generated. No interim analysis will be performed.

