### Recruitment

#### Inclusion Criteria

In Japan, smoking cessation treatment is covered by health insurance if it is the patient’s first time undergoing the treatment or if more than 1 year has passed since the last treatment. Accordingly, this study included patients covered by health insurance [11] and who met all of the following criteria based on the diagnosis and tests before starting treatment for smoking cessation:

Smokers with nicotine dependence (Fagerström Test for Nicotine Dependence [FTND] score of 5 points or more) who wish to quit smoking.Patients with depression with SDS scores of 39 to 59, based on the self-report questionnaire for assessing propensity to depression.Patients aged 20 to 79 years at the time of the informed consent procedure.Outpatients.Patients whose informed consent has been obtained in writing.

This study aims to include 100 participants in the analysis.

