#### Exclusion Criteria

Patients will be excluded from this study if it is determined that they meet any one of the following exclusion criteria based on their diagnosis or test results prior to the start of the study:

Patients whose condition is inappropriate for aromatherapy, that is, those suffering from shock, severe disease states, poor respiratory status, feeling of nausea, or vomiting, etc.Patients who habitually practice aromatherapy.Patients who are unable to smell the aromas of essential oils due to olfactory dysfunction.Patients with a history of epileptic seizures.Patients who are currently on medication for a psychiatric or psychosomatic condition.Patients with an SDS score of 53 points or higher, which is indicative of underlying depression and need for psychiatric consult, and those prescribed medication for a psychiatric and psychosomatic condition [33].Patients with current symptoms of drug allergy.Patients who are pregnant, are lactating, or intend to become pregnant during the study period.Other patients who are deemed to be unsuitable according to the attending physician (patients with severe dementia, poor compliance, etc).

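### Within-group paired t tests on SDS start from the score used to select patients, and the plan does not say that only the between-group contrast can support an aromatherapy effect

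*Protocol article*

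**What the plan says.** Inclusion Criteria admit "Patients with depression with SDS scores of 39 to 59", while Exclusion Criteria remove "Patients with an SDS score of 53 points or higher". Applied together, these leave a window of 39 to 52. Study Design says that this study and the earlier yokukansan trial, which supplies the control group, both took only scores of 39 to 59.

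The primary outcome is the change in SDS and POMS, "which will be evaluated for the period from the pretreatment screening to 4 weeks and 12 weeks after the start of aromatherapy". The Procedures place the screening SDS at enrollment, up to four weeks before the start.

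In Statistical Analysis the rule for significance is "Statistical significance was set at *P*<.05". SDS and each POMS subscale are tested for a difference between baseline and week 12 by a paired t test, and this is done separately "in the aromatherapy group of this study and in the standard treatment group of our previous study". The section then adds a two-way ANOVA of the group interaction in change from baseline to week 12. No order of precedence is given between the paired tests and the interaction. Hypothesis and Objective ties the aim to adding aromatherapy to standard treatment and to comparison with the historical control.

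**The concern.** When patients are chosen because a score is high and the same score is the baseline, the next measurement tends to be lower even if nothing has changed. All patients also receive cessation medication and counselling, and the article itself expects mood to shift during quitting. The paired null hypothesis, no change since screening, can therefore be false without any contribution from aromatherapy.

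The Objective makes the result the basis for deciding on a phase III trial, and the Limitations section describes the study as designed to confirm efficacy and safety. A small within-group P value could be carried into that decision as evidence for aromatherapy, and nothing in the analysis text rules this out.

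**Working it through.** **Inputs from the article.** SDS window 39–59, or 39–52 if the exclusion is applied; n=100 planned, 76 recruited by May 2022; alpha 0.05, taken as two-sided. The sample size was set by feasibility, so there is no power figure to reproduce.

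**Assumed, because the article does not give them.** SDS mean μ among all clinic smokers 38 to 45; SD σ = 8; correlation ρ between screening and week 12 of 0.6 to 0.8; bivariate normal scores; no true change. Integer limits are widened by half a point (38.5 to 59.5, or 38.5 to 52.5).

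**Formulas.** Let m and v be the mean and variance of the selected (truncated normal) screening scores.
- Expected fall = (1 − ρ)(m − μ)
- Variance of change = (1 − ρ)²v + (1 − ρ²)σ²
- Rejection rate: noncentral t, n − 1 degrees of freedom, noncentrality √n × fall / SD of change

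**Example: μ = 42, ρ = 0.6, window 39–59, n = 100.** m = 45.98 and √v = 4.98. Fall = 0.4 × 3.98 = 1.59 points. Variance = 0.16 × 24.83 + 0.64 × 64 = 3.97 + 40.96 = 44.93, so SD = 6.70. Noncentrality = 10 × 1.59 / 6.70 = 2.38. Rejection rate: 65%, against a nominal 5%.

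**Rejection rates of the paired SDS test with no true change, n = 100:**

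| Clinic mean | 39–59, ρ 0.6 | 39–59, ρ 0.8 | 39–52, ρ 0.6 | 39–52, ρ 0.8 |
|---|---|---|---|---|
| 38 | 97% | 76% | 94% | 66% |
| 40 | 87% | 56% | 73% | 41% |
| 42 | 65% | 36% | 37% | 20% |
| 45 | 26% | 15% | 6% | 5% |

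At μ = 40 and ρ = 0.7, the rate for 39–59 is 75% at n = 100 (a simulation with rounded scores gave 75.2%) and 63% at n = 76. For 39–52 it is 58% and 47%.

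**The planned interaction test under the same null** (100 against 220 controls, μ = 40, σ = 8, ρ = 0.7, simulated): type I error 5.4% when both groups share the 39–59 window. If aromatherapy patients stop at 52 and controls at 59, it is 7.3%, with a mean shift of 0.29 points against aromatherapy.

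**Reading the two paired tests against each other.** Take the same true change of 0.3 SD in both groups. Power at n = 100 is 0.84.
- Control of 220 (the size stated in Study Design): power 0.99. One test is significant and the other not in 16% of trials, and significant in aromatherapy only in under 1%.
- Control of 50 (an assumption): power 0.55. Discordance = 0.84 × 0.45 + 0.16 × 0.55, about 47%.

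**The case against.** The strongest reply is that the article already plans a valid contrast. The interaction ANOVA compares change between groups that Study Design says were selected on the same SDS range, so regression to the mean largely cancels. A reader might infer that the plan leaves regression to the mean uncontrolled, or that the paired test is the primary analysis. The text supports neither: the interaction test is there, no analysis is ranked first, and the section speaks of comparison with the control before it mentions the paired tests.

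Other parts of the reply also stand. The size depends on a clinic mean, SD and correlation that are not given, and with a mean near the middle of the 39–52 window the paired test is close to nominal. Regression to the mean acts directly on SDS only. POMS was not a selection variable and is affected only through its correlation with SDS. The temporary worsening that the article expects could offset a fall. A high discordance between the two paired tests depends on a small control group that the article does not state.

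The article also calls itself exploratory and concedes limited rigor and no randomization. These admissions do not mention selection on the outcome, and they do not say that within-group P values are uninformative about aromatherapy. An offsetting worsening would leave the paired result just as hard to interpret.

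**Conclusion.** The point holds in a limited form. The paired SDS test cannot isolate the effect of adding aromatherapy, because selection on the baseline score and the standard-treatment course both enter the change. That conclusion needs no numerical assumption. The size does: about 36–97% false rejection for 39–59 and 20–94% for 39–52 with a clinic mean of 38 to 42, SD 8, correlation 0.6 to 0.8 and n = 100, and about 5–26% with a mean of 45. It would be too strong to say that the paired test will nearly always be significant.

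The defect is that the analysis text puts an uninformative test beside an informative one and does not say which supports efficacy. The conflicting upper SDS limits add a smaller problem, since they leave open whether both groups cover the same range. The between-group contrast still carries the usual bias of a historical control, which the article acknowledges.

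**What to change.** In Statistical Analysis:

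- Name the between-group contrast in change, adjusted for baseline score (ANCOVA in place of the unadjusted interaction), as the only basis for efficacy statements.
- Report within-group changes in both groups as means with confidence intervals, without P values or efficacy wording.
- Reconcile the upper SDS limit in Study Design and Inclusion Criteria (59) with Exclusion Criteria (53 or higher excluded), so that the two groups can be compared over the same range.
- Use an SDS score from the day of treatment start as baseline only if it is a separate repeat measurement and exists in both groups. Secondary Outcomes lists SDS among the day-of-start items, but the article allows consent on the day of briefing, so the two scores may be one and the same. Nothing is said of a second score in the control group.

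The cost is a change of wording and analysis, with no new data. The downside is a less favourable headline than a pre-post P value.

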## Methods

### Study Design

This is a pre-post single-arm clinical trial conducted at the National Hospital Organization Kyoto Medical Center in Japan. Patients in this study who visited the smoking cessation clinic at the medical center to receive smoking cessation treatment were assessed using the Zung Self-Rating Depression Scale (SDS) and were classified into two groups: the healthy group (SDS score ≤38) and the depressed group (SDS score = 39-59). Patients in the depressed group are considered to have depressive tendencies. Patients who provide consent will be included in this study, with a target sample size of 100. Smokers with depression will be subjected to aromatherapy during smoking cessation treatment for 12 weeks. Changes in the SDS score and the Profile of Mood States (POMS) score from pretreatment screening to 4 and 12 weeks after the start of aromatherapy will be evaluated. This study will also compare the aromatherapy group with the standard treatment group from a previous study entitled “A Randomized, Multi-center, Double-Blind, Placebo-Controlled Trial for the Effects of Yokukansan on Depressive or Neurotic Smoking Patients during Smoking Cessation Therapy” (University Hospital Medical Information Network [UMIN] ID: 000027036); this group will act as a control group (ie, historical control group). In both studies, only smokers with SDS scores of 39 to 59 were included in the study, and the study subjects were randomly assigned to either the yokukansan group (ie, yokukansan plus standard treatment) or the control group (ie, standard treatment), with 220 subjects in each group. Changes in SDS and POMS scores from pretreatment screening to 4 and 12 weeks after the start of treatment, as well as the rate of successful smoking cessation, will be evaluated. Furthermore, an exploratory analysis on the efficacy of aromatherapy will also be conducted (eg, analyzing the correlation between essential oil preference and smoker information items at the first visit and the changes in essential oil preferences over time).

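### P<.05, if read as study-wide, is applied to comparisons with one historical trial using tests that allow for no trial-to-trial drift, so their false-positive rate is unknown and may exceed 5%

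*Protocol article*

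**What the plan says.** All of the relevant text is in the Statistical Analysis section of the protocol article, except the control-arm size, which is under Study Design.

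- Scores at baseline and week 12 "will be compared using paired-samples *t* tests in the aromatherapy group of this study and in the standard treatment group of our previous study". The criterion comes directly after this: "Statistical significance was set at *P*<.05".
- For change from baseline to week 12, "a two-way analysis of variance will be used analyze the interaction between the standard treatment group and the aromatherapy group". The same method is to "compare changes in SDS and POMS scores before and after smoking cessation between the historical control group and the aromatherapy group of this study".
- For the binary outcome: "We will also compare the successful smoking cessation rates for a period of 12 weeks from the start of treatment", again between the standard-treatment and aromatherapy groups.
- The control is one arm of one trial: "We will perform a comparison of the aromatherapy group with the standard treatment group from our previous study". Study Design gives the arms of that trial "with 220 subjects in each group". On the local share, Statistical Analysis says "For the yokukansan study, 100 patients were registered in our hospital".

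The section states no separate level, between-trial term, discounting or descriptive-only status for the historical comparisons. It plans no confidence intervals and gives no SD.

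**The concern.** Every aromatherapy patient comes from one trial and every control from another, so treatment group and trial are fully confounded. Mean change under identical care can differ between trials because of staff, calendar time, procedures and who volunteers. Recruiting more patients does not reduce that component, and a test built on patient-level error does not include it.

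The article itself shows that the settings differ. By its title, the earlier trial was multicentre, double-blind and placebo-controlled. This one is single-centre and single-arm, and its recruitment was extended because of COVID-19 (Study Design; Study Period).

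The within-group paired tests cannot attribute a change to aromatherapy. The historical comparison is the only planned analysis that could, and the abstract's Objective says the study is to help decide whether a phase III trial is reasonable. A difference that passes P<.05 could be read as an aromatherapy effect when it is drift between trials.

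**Working it through.** **Inputs from the article.** Nominal level .05 (sidedness not stated, taken as two-sided). 76 patients recruited by May 2022, 100 planned. 220 per arm in the earlier trial. 100 patients of that trial registered at this hospital, so about 50 local controls if the arms were split equally (assumption).

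**Inputs that must be assumed.** SD of SDS change = 8. The group-by-time interaction is tested on change scores, that is, in repeated-measures form. The drift SD, d, is the SD of the difference in mean change between the two trials when the treatments have the same effect.

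**Formulas.**
- SE = 8 × √(1/76 + 1/220) = 8 × 0.1331 = 1.06 points.
- With drift, the true variance of the difference is SE² + d², but the test still uses SE. Actual two-sided error = 2 × [1 − Φ(1.96 × SE / √(SE² + d²))].
- Half-width of a 95% interval that includes drift = 1.96 × √(SE² + d²).

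**Step 1: the plan's own figure.** At d = 0 the formula returns 5.0%, so the stated level is reproduced when there is no drift.

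**Step 2: drift added (76 versus 220, SD 8).**

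| d (SDS points) | Actual error rate | Half-width including drift |
|---|---|---|
| 0 | 5.0% | 2.09 |
| 0.25 | 5.6% | 2.14 |
| 0.5 | 7.6% | 2.30 |
| 1 | 15.3% | 2.86 |
| 2 | 35.7% | 4.44 |
| 3 | 51.2% | 6.24 |

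Example, d = 1: √(1.133 + 1) = 1.460; 1.96 × 1.064 / 1.460 = 1.43; 2 × [1 − Φ(1.43)] = 15.3%.

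**Step 3: sensitivity to the assumed SD.** At d = 2, an SD of 6 gives 46.7% and an SD of 10 gives 27.8%.

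**Step 4: planned sample size, free of the SD assumption.** Let each trial's mean carry its own deviation τ, in SDs of change, so that d² = 2τ². For 100 versus 220, τ of 0.02, 0.05, 0.10 and 0.20 gives 5.6%, 9.1%, 20.3% and 44.2%. A simulation with 40,000 replicates gave 5.1% at τ = 0, and 9.4%, 20.4% and 44.3% at τ = 0.05, 0.10 and 0.20.

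**Step 5: same-hospital controls only (76 versus about 50).** SE = 8 × 0.1821 = 1.46. Drift SDs of 1, 2 and 3 give 10.6%, 24.9% and 39.2%. These rates hold drift fixed, so the fall from step 2 comes only from the larger SE. If a shared hospital also reduces drift, the rates are lower.

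**Step 6: cessation rate.** Assume 60% in controls. SE = √(0.6 × 0.4 × (1/76 + 1/220)) = 0.065. Drift SDs of 5 and 10 percentage points give 12.0% and 28.4%.

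**The case against.** **The size is assumed.** A reader might infer that the true false-positive rate is far above 5%. The article does not support that. It gives no between-trial variation, and one historical trial cannot supply an estimate. At drift of 0.25 points the rate is barely above nominal. This objection stands, so the excess can be given only as a range.

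**No intervals are planned.** A reader might also infer that the plan's intervals are too narrow, but it states none. What remains is conditional: an interval built from the same SE would be too short if drift exists.

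**The criterion follows the paired t tests.** The P<.05 sentence comes straight after the within-group tests, whose standard errors are not affected in this way, and before the ANOVA. Applying it to the historical comparisons is an inference, though a natural one, since it is the only criterion stated.

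**The ANOVA form is open.** If the ANOVA ignored the pairing within patients, it would be conservative at zero drift: 2 × [1 − Φ(1.96 / √(1 − 0.5))] = 0.6% at an assumed correlation of 0.5. That would offset some inflation. The article does not say which form is meant.

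**The weakness is disclosed.** The abstract's Conclusions deny rigorous validation, Limitations says the study is not a randomised trial, and no sentence makes P<.05 the rule for starting phase III. This lowers the weight. It does not change the criterion or tell a reader how much drift would overturn a result. Limitations also describes the study as designed to confirm efficacy and safety.

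**This is bias, and belongs in an analysis plan.** The differences in setting may be systematic rather than random. A fixed shift has a similar consequence: 0.1 SD (0.8 points at SD 8) gives 11.7% for 76 versus 220. A tipping-point analysis serves both cases. Variance terms can indeed be left to an analysis plan. The point here is the unqualified criterion that the article does fix.

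**Conclusion.** The point holds in a limited form. If P<.05 applies study-wide, the ANOVA interaction and the cessation comparison hold a 5% false-positive rate only when there is no trial-to-trial drift, and the article gives reasons to doubt that. The actual rate is unknown. On the stated assumptions (SD of change 8, change-score ANOVA, 76 versus 220) it runs from near nominal for drift of a quarter of a point to about half for drift of 3 points. It is substantially above 5% only from drift of roughly 1 SDS point upward. The paired t tests are outside the point. It is worth correcting because the remedy is cheap and bears on the only comparison that could attribute an effect to aromatherapy.

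**What to change.** In the Statistical Analysis section:

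1. State that all comparisons with the historical control (SDS, POMS and cessation) are descriptive and are not judged by P<.05.
2. Report each difference with a 95% interval labelled as excluding between-trial variation.
3. Add a tipping-point line: the drift in control mean change (SDS or POMS points) or in cessation rate (percentage points) that would remove the finding. For an observed difference D whose interval excludes zero, this is |D| − 1.96 × SE. It needs no estimate of between-trial variance.
4. Show a sensitivity table over a stated range of assumed between-trial SDs, with the same-hospital control subset alongside. The between-centre SD in the earlier trial may inform the range. It should not be called a lower bound, because differences between centres may exceed drift over time at one hospital, and raw centre means also carry sampling error.

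The cost is a few lines of text, one extra table, and fewer results that can be called significant. The group data for the main comparison are already part of the plan. The centre-level items need centre identifiers from the earlier trial. When the article was published, the analyses were still to come.
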